#### Identification and Recruitment of Patients

Before introducing the complex intervention, each participating practice will engage in an intensive, 2-week period of patient recruitment, an approach we found most effective in previous qualitative work with this population [19]. This 2-week period will be supported by a member of the research team and will aim to: (1) establish a “disease” register of patients, (2) obtain contact details for and informed consent from eligible patients, (3) review the clinical records of patients who consent to participate in the study, and (4) collect baseline data, including patient demographics and current care process/outcome measures from clinical records.

Patients will be eligible to participate if they are 18 years of age or older, receiving addiction treatment/care (eg, methadone), or known problem drug user, and attending a participating general practice for general medical care. They will be excluded from the study if they have language difficulties (ie, unable to speak, read, and write English well enough to complete study questionnaires), are acutely intoxicated, and/or are cognitively impaired (including severe mental health illness) to the extent that they are unable to provide informed consent to participate.

Systematic random sampling of patients in participating practices is difficult in studies among this population [25]. Hence, a standardized nonprobability sampling framework will be used to identify *consecutive* patients from each practice on whom data will be collected for the purpose of the study. Potential patient selection bias will be assessed in the exploratory data analysis, by comparing the sociodemographics of the included patients with all patients, who were identified as problem drug users, in each practice.

Patients who consult a GP taking part in the study, and who in the clinical opinion of the GP are eligible to participate in the study (see inclusion criteria above), will be given written information on the study. Those interested in participating will be invited to meet a researcher who will be at the practice during the recruitment period. At this meeting, interested patients will be given further information on the study and will have an opportunity to ask questions from the researcher. If patients consent to participate, they will be asked to sign a consent form and complete a self-/interviewer-administered questionnaire that includes problem alcohol use and other outcome measures, if necessary with the assistance of the researcher at T1 (ie, Time 1, at baseline) and T2 (ie, Time 2, at 3 months follow-up). This applies to patients in both the intervention and control groups.

Following completion of the self-/interviewer-administered questionnaire with the researcher, patients in the intervention practices will be screened for problem alcohol use and delivered the brief intervention by their GP/practice team (at their earliest convenience). Patients in the control arm will receive the “Less is more” leaflet (a guide to rethinking your drinking, HSE, 2008) from the researcher. A “thank you” letter will be sent to all GPs and patients within 2 weeks of receiving completed study instruments/intervention. A reminder letter will be sent to all GPs and patients 5 weeks before the follow-up assessments, informing them of the anticipated time/date of their appraisal. Figure 1 presents the CONSORT diagram of participant flow and follow-up.

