**Methods:**

Psychosocial intervention for alcohol use among problem drug users (PINTA) is a pilot feasibility study of a complex intervention comprising SBI for problem alcohol use among problem drug users with cluster randomization at the level of general practice, integrated qualitative process evaluation, and involving general practices in two socioeconomically deprived regions.
Practices (N=16) will be eligible to participate if they are registered to prescribe methadone and/or at least 10 patients of the practice are currently receiving addiction treatment. Patient must meet the following inclusion criteria to participate in this study: 18 years of age or older, receiving addiction treatment/care (eg, methadone), or known to be a problem drug user. This study is based on a complex intervention supporting SBI for problem alcohol use among problem drug users (experimental group) compared to an “assessment-only” control group. Control practices will be provided with a delayed intervention after follow-up. Primary outcomes of the study are feasibility and acceptability of the intervention to patients and practitioners. Secondary outcome includes the effectiveness of the intervention on care process (documented rates of SBI) and outcome (proportion of patients with problem alcohol use at the follow-up). A stratified random sampling method will be used to select general practices based on the level of training for providing addiction-related care and geographical area. In this study, general practitioners and practice staff, researchers, and trainers will not be blinded to treatment, but patients and remote randomizers will be unaware of the treatment.

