## Methods

### Overview of Study Design

Psychosocial intervention for alcohol use among problem drug users (PINTA) is a pilot feasibility study of a complex intervention to promote SBI for problem alcohol use among problem drug users, with cluster randomization at the level of general practice, and integrated qualitative process evaluation, involving general practice in two regions.

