### Study Population

#### Recruitment and Random Selection of Practices

The following practices will be invited to participate, given written information on the study and their interest in participating:

All practices in two regions—Health Services Executive (HSE) Midwest and Dublin Mid-Leinster regionsAll practices that have been involved in previous related research with our group [18,23-29]General practices in the study regions that are affiliated with two of the Ireland’s six medical schools [30,31]

Practices will be eligible to participate if they are registered to prescribe methadone and/or have at least 10 patients currently receiving addiction-related care.

Of those who confirm their *interest* in the study and who are eligible to participate, a stratified random sampling technique will be used to select 16 practices.

Sampled GPs will be contacted about their participation, given further information on the study (eg, what their involvement will entail) and consulted about patient recruitment. The research team will telephone those not replying. Each practice will be visited by the principal investigator or lead researcher and provided with the information about the research program.

To ensure comparability between intervention and control groups for key practice characteristics, a restricted allocation involving stratified approach to randomization will be adopted. Prior to randomization, GPs who express their interest in participating will be grouped according to the level of training in providing addiction-related care (level 1 and 2), geographical location (Dublin/Midwest), with 16 randomly selected GPs using an independent remote randomization service.

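### Patient recruitment is timed against the start of the intervention, not against disclosure of the practice's allocation, and the planned selection check is not designed to show enrolment that differs by arm

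*Protocol article*

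**What the plan says.** All references are to the protocol article.

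- **Unit of randomisation** (Overview of Study Design): the study is a pilot "with cluster randomization at the level of general practice, and integrated qualitative process evaluation, involving general practice in two regions".
- **Blinding** (Abstract, Methods): "general practitioners and practice staff, researchers, and trainers will not be blinded to treatment, but patients and remote randomizers will be unaware of the treatment".
- **Before randomisation** (Recruitment and Random Selection of Practices): the one step tied explicitly to that point is the stratification of practices: "Prior to randomization, GPs who express their interest in participating will be grouped according to the level of training in providing addiction-related care", together with location.
- **Timing of patient recruitment** (Identification and Recruitment of Patients): "Before introducing the complex intervention, each participating practice will engage in an intensive, 2-week period of patient recruitment". The register, consent, record review and baseline data all fall in this period.
- **Who controls entry** (same section): written information goes to patients "who in the clinical opinion of the GP are eligible to participate in the study". Interested patients then meet a researcher on site, who takes consent and helps with the T1 questionnaire where needed. Patients are to be identified consecutively under a standardised framework.
- **What follows baseline** (same section): "Following completion of the self-/interviewer-administered questionnaire with the researcher, patients in the intervention practices will be screened for problem alcohol use" and receive the brief intervention from their practice team. Control patients are given a drinking leaflet by the researcher.
- **Selection check** (same section): selection bias will be assessed "by comparing the sociodemographics of the included patients with all patients" identified as problem drug users in each practice.

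**The concern.** Randomising practices balances the practices. It protects the comparison of patients only if those who enter do so without regard to the arm. When the people who invite and consent patients know the arm, recruitment can drift. A GP about to deliver an alcohol intervention has a reason to think first of known drinkers or of patients likely to cooperate; a GP in a control practice has less reason to.

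The protocol's timing rule does not close this route. Recruitment that comes before the intervention can still come after the arm is known, and the text does not say which applies.

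This matters even in a pilot. The introduction (Phase 2: Exploratory Study) says that the study should supply patient recruitment rates, the intraclass correlation coefficient and the likely effect for a definitive trial. The sample size section uses the proportion who reduce drinking to plan that trial's size and follow-up. Enrolment that differs by arm would feed into each of these. Patient recruitment is also a feasibility measure, and feasibility is a primary outcome.

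**Working it through.** **1. The order of events, passages side by side.** The recruitment section fixes recruitment before intervention. The practice-selection section fixes stratification before randomisation. Neither links patient recruitment to randomisation or to disclosure. Two orders therefore fit the text:

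- (a) stratify, recruit patients, disclose the arm, intervene;
- (b) stratify, disclose the arm, recruit patients, intervene.

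Order (a) protects against arm-dependent enrolment; order (b) does not. Two details lean towards (b) without proving it: the researcher who collects baseline data also gives control patients the leaflet, and the Control Intervention section describes identification and recruitment by practices already labelled by arm.

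**2. What the selection check can show.** It names sociodemographics only, within practice, and compares included patients with a list that contains them. It names no drinking or motivation variable and no contrast between arms. AUDIT and the Readiness Ruler are collected at baseline in both arms, but are not part of this check.

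**3. The plan's own figures.** 160 / 16 = 10 patients per practice. The 20% qualitative sample of 16 implies 16 / 0.20 = 80 intervention patients, half of 160. These agree. The 160 rests on pilot-study guidance rather than a power formula, so there is no power figure to reproduce.

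**4. Illustration: how far enrolment could shift baseline prevalence.** Input from the protocol: p = 0.35 (the national study of methadone patients). Assumption: in one arm, problem drinkers are r times as likely to be enrolled as other patients. Then p' = p·r / (p·r + 1 − p).

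The last two columns give the power of a two-sided 5% comparison of baseline prevalence with n = 80 per arm (normal approximation). For an assumed ICC of 0.05, the design effect is 1 + 9 × 0.05 = 1.45, so n = 80 / 1.45 = 55.2.

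| r | p' | gap (points) | power, ICC 0 | power, ICC 0.05 |
|---|---|---|---|---|
| 1.25 | 0.4375 / 1.0875 = 40.2% | 5.2 | 10% | 8% |
| 1.5 | 0.525 / 1.175 = 44.7% | 9.7 | 24% | 18% |
| 2.0 | 0.70 / 1.35 = 51.9% | 16.9 | 58% | 43% |

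Even a direct baseline comparison would often miss such a shift, so prevention is worth more than a later check.

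**5. Illustration: what reaches follow-up with no treatment effect.** Assumptions: 60-80% of problem drinkers persist, 5% of other patients become problem drinkers, and the comparison is unadjusted. Bias = gap × (persistence − incidence).

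- 10-point gap: 0.10 × (0.60 − 0.05) = 0.055; 0.10 × (0.80 − 0.05) = 0.075.
- Range for gaps of 5 to 15 points: 0.05 × 0.55 = 0.0275 to 0.15 × 0.75 = 0.1125, or about 3 to 11 points.

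**The case against.** The strongest reply is that the order is open, not wrong. A reader might infer from the leaflet sentence that the arm is known at the recruitment visit. The text does not say so: it gives no time or place for the leaflet, and unblinded to treatment need not mean informed during recruitment. The CONSORT diagram might settle the order, but it is not available in the text reviewed. This part of the reply stands, and the point is limited accordingly: the protocol permits enrolment after disclosure; it does not prescribe it.

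GP discretion is also limited. Patients are to be taken consecutively, the GP's judgement concerns eligibility, and drinking is not an entry criterion. The register requirement and the €50 payment apply in both arms. These are real but partial safeguards, since GP opinion and patient interest still filter who enters.

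It would go too far to say that the selection check cannot detect anything. It can show sociodemographic selection, its results can be grouped by arm because each practice belongs to one arm, and baseline AUDIT will exist for both arms. What remains is that the check as stated does not use these data for that purpose.

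Nor is the 20% consent target at risk. The sample size section defines it as invited GPs who confirm interest, and that precedes randomisation. Only patient-level recruitment could be affected.

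Finally, effectiveness is a secondary outcome and the protocol disclaims power for it. That lowers the severity. It does not remove the point, because lack of power widens the interval around a planning estimate, whereas selection moves the estimate itself.

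**Conclusion.** The point holds as a gap in sequencing with an incomplete check behind it, at moderate severity. Followed as written, the plan allows unblinded GPs and researchers to enrol patients once the arm is known, and its stated selection check is not designed to show the result.

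It would be wrong to conclude that recruitment will follow disclosure, or that the effect estimate will be biased by any particular amount. The 5.5 to 7.5 points for a 10-point gap, and the wider range of about 3 to 11 points, rest on assumed gaps, persistence and incidence. Only the 35% prevalence comes from the protocol. Adjustment for baseline AUDIT could reduce the bias arising from measured drinking, but not that from unmeasured differences. The protocol states no target effect against which to judge these figures.

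**What to change.** 1. State the order. Release each practice's allocation to the practice and the researcher only after its 2-week window has closed and its list of consented patients and T1 data are locked. The remote randomisation service already planned can hold the allocation until then.
2. Send arm-specific material after release. The control leaflet could go with the thank-you letter that is already planned.
3. Extend the selection check to included versus not-included patients, by arm, and show numbers invited, numbers consenting and baseline AUDIT by arm. AUDIT is already collected; the counts need a simple recruitment log.

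The cost is modest. Training for intervention practices is scheduled about two weeks later, and control patients receive the leaflet after the visit rather than from the researcher in person. Recruitment already precedes the intervention, so no further patient visit is needed. If the intended order is already recruitment before disclosure, step 1 reduces to one clarifying sentence.

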## Introduction

### Overview

Problem alcohol use is associated with adverse health and economic outcomes, all the more so among problem drug users (eg, individuals currently using illicit drugs or trying to abstain from other illicit drugs such as benzodiazepines, cocaine, or heroin) [1,2]. Such alcohol use may decrease in response to psychosocial interventions whose benefits have been demonstrated in general adult populations. For example, a comprehensive review by Raistrick et al presented data on the effectiveness of many such interventions, including screening, further assessment, brief interventions, and alcohol-focused specialist treatment [3].

Primary care may have an important role in addressing problem alcohol use among problem drug users. Its potential impact on screening for alcohol problems and providing appropriate interventions in the general population has been described [4], although a recently published randomized trial indicates that more intensive primary-care-based interventions provide little by way of additional benefit to patient information alone [5]. Internationally, screening and brief interventions (SBI) are recommended as a treatment of choice for reducing alcohol use among problem drinkers in primary care [6,7], but these have not been tested in people who are addicted to other substances and who attend primary care [8]. It is important to address this issue because of the serious complications associated with problem alcohol use in this population, that is, the potential to increase the likelihood of a relapse to problem drug use, medical/psychological complications, liver disease, and so on [1,2].

Similar to other evidence-based interventions, the evidence on SBIs translates slowly into practice [9-11], and the findings from implementation studies are contradictory. For example, while a systematic review of interventions focused on increasing the use of SBI for hazardous alcohol consumption in primary care recommended complex, multicomponent strategies [12], a recent trial concluded that such a “tailored, multifaceted program aimed at improving general practitioner (GP) management of alcohol consumption” failed to show an effect and proved difficult to implement [13]. This also contradicts the conclusions of a recent paper, “real world evidence supports theory” of SBIs [14].

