### Intervention

#### Overview

A staggered intervention design will be adopted, whereby participating practices randomized to the intervention arm of the study will be provided with the complex intervention for the duration of the study period, while practices randomized to the control arm of the study will provide usual care to patients for the duration of the study and will be provided with the complex intervention thereafter (ie, delayed intervention). Such an approach was used successfully in our previous cluster randomized controlled study to improve screening for hepatitis C among problem drug users attending general practice in Ireland [25].

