#### Control Intervention

All practices (control and intervention arms) will be required to establish a “disease” register of “problem drug users” before the study onset. They will identify potential participants and recruit them for the study. At this stage, participants will be asked to sign an informed consent form. The research team will conduct interviews (telephonic or in person) to determine problem alcohol and other drug use and demographic details at baseline and at 3 months follow-up. Researchers will facilitate data collection (including morbidity and primary/secondary care utilization) from clinical records. Participating practices will be offered €50 per patient recruited to study upon receipt of completed data [34].

We consider the above engagement with practices as close to “usual care” as possible while still allowing evaluation of the complex intervention. To enable the development of a practice register of people with problem drug use, clinical records and prescribing information will be reviewed. For practices who use electronic patient records, an International Classification of Primary Care disease code (P19) will be assigned to patients who meet the criteria of European Monitoring Center for Drugs and Drug Addiction for problem drug use. For practices who use paper records, this register will be developed in a hard copy.

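### The comparator is labelled assessment-only, but control patients are also to receive an alcohol information leaflet

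*Protocol article*

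**What the plan says.** Four places in the protocol article describe the control condition.

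- Abstract, Methods: the intervention is for "problem drug users (experimental group) compared to an “assessment-only” control group".
- Intervention, Overview: "practices randomized to the control arm of the study will provide usual care to patients for the duration of the study", followed by a delayed intervention.
- Control Intervention: this section covers the practice register, recruitment and consent, research interviews at baseline and 3 months, and data collection from clinical records. It adds: "We consider the above engagement with practices as close to “usual care” as possible while still allowing evaluation of the complex intervention". It mentions no leaflet.
- Identification and Recruitment of Patients: control-arm patients are to receive the *Less is more* "leaflet (a guide to rethinking your drinking, HSE, 2008) from the researcher". For the other arm, the same paragraph says that "patients in the intervention practices will be screened for problem alcohol use and delivered the brief intervention by their GP/practice team", with no mention of a leaflet.

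The outcome concerned is secondary and is given in the abstract as "outcome (proportion of patients with problem alcohol use at the follow-up". Phase 2: Exploratory Study says that the pilot will estimate the likely effect of the intervention for a definitive cluster trial. Power Calculations and Sample Size Estimates says that the proportion of patients who cut their drinking will be used to predict that trial's sample size. It also says that the pilot is not powered for effectiveness.

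**The concern.** A between-arm estimate means something only in relation to a named comparator. A guide to rethinking one's drinking, handed over by study staff, is not assessment, and its subject is the behaviour that the drinking outcome measures. Someone who replicates the control from the abstract and the Control Intervention section would leave the leaflet out. Someone who reads the effect estimate under the abstract's label would take it as a difference from assessment alone.

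What is at stake is the interpretation of the secondary drinking estimate and its later use for planning. If the definitive trial were designed with an assessment-only control but used an estimate obtained against a leaflet, the planning difference would belong to another contrast.

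**Working it through.** No stated figure is in dispute, and the article gives no power, significance level or effect size to reproduce. The main check is a comparison of the texts.

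**Step 1: what each label allows.**

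| Place | Control described as | Compatible with a researcher-given leaflet? |
|---|---|---|
| Abstract, Methods | assessment only | No |
| Intervention, Overview | practices give usual care | Yes: it describes the practices, and the leaflet comes from the researcher |
| Control Intervention | register, consent, interviews, record review | Incomplete: the leaflet is absent from the section meant to define the control |
| Identification and Recruitment of Patients | leaflet from the researcher | This is the source of the leaflet |

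The direct contradiction is with the abstract's label. Control Intervention omits the leaflet. The usual-care wording can stand as a description of what the practices do.

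**Step 2: the contrast that results.** Let pA, pL and pI be the proportions with problem alcohol use at follow-up under assessment only, under assessment plus leaflet, and under the complex intervention.

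- Contrast under the abstract's label: pA − pI.
- Contrast as described: pL − pI = (pA − pI) − (pA − pL).

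The gap between the two is the leaflet's own effect, pA − pL. It is zero if the leaflet does nothing. If the leaflet lowers problem use, the observed difference is smaller than the labelled one by exactly that amount. This takes the text at its word that only control patients get the leaflet. If intervention patients also received it, the contrast would be the intervention added to a leaflet, which again is not the labelled one.

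**Step 3: which outcomes are exposed.** Feasibility and acceptability rest on recruitment, participation and retention rates, interviews and questionnaires, not on a between-arm drinking contrast. Documented rates of screening and brief intervention are a practice behaviour, so a leaflet from the researcher should affect them little. The exposed items are the drinking estimate and the planning values taken from it, including any control-arm proportion.

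**Step 4: how the gap would carry into planning (illustration only).** From the article: 35% of 196 methadone patients in an earlier national study had problem alcohol use, taken here as pA. Assumed, with no source in the documents: pI = 20%, and a leaflet effect of 0 to 7.5 points. With two-sided 5% significance, 80% power, individual randomization and no design effect, and p̄ = (pL + pI)/2:

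n per arm = [1.96·√(2p̄(1−p̄)) + 0.8416·√(pL(1−pL) + pI(1−pI))]² / (pL − pI)²

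| Assumed leaflet effect (points) | pL | pL − pI (points) | n per arm |
|---|---|---|---|
| 0 | 35% | 15 | 138 |
| 2 | 33% | 13 | 180 |
| 5 | 30% | 10 | 294 |
| 7.5 | 27.5% | 7.5 | 505 |

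The first row is the case where the label makes no difference. The table shows that the choice of contrast can matter for planning. It does not estimate how much it matters here.

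**The case against.** The best defence is that this is one loose label in an abstract. The leaflet is openly disclosed in the Methods. Usual care is attributed to the practices, and the remark about staying close to usual care refers to engagement with practices, so neither statement is contradicted by something a researcher hands out. That stands, and it limits the contradiction to the abstract's label and the gap in the Control Intervention section.

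It can also be said that any harm to the definitive trial is conditional. If that trial uses the same leaflet control, the pilot's contrast is the right one, and the documents do not say which comparator it will use. That stands too. So does the point that the article condenses a fuller protocol and that its flow diagram is not shown. Silence about a leaflet in the intervention arm is therefore not proof that none is given, and the leaflet sentence states no time of delivery.

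Two stronger readings are tempting, and the documents support neither:

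- A reader might infer that the leaflet is known to be active, because the Introduction cites a trial in which "more intensive primary-care-based interventions provide little by way of additional benefit to patient information alone". That finding fits equally well with neither approach having an effect. The Introduction also says that these interventions have not been tested in people addicted to other substances who attend primary care. It therefore says nothing firm about the size of a leaflet effect here.
- A reader might infer that the leaflet makes a null result uninterpretable. The pilot disclaims power for effectiveness, so a null would be inconclusive against any comparator. The drinking questionnaire is also given in both arms at baseline and 3 months, so improvement in both arms would be visible, although its cause could not be separated.

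None of this reconciles an assessment-only label with a control that includes an alcohol leaflet.

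**Conclusion.** The comparator label is wrong as written. On the current text, the drinking contrast is the complex intervention against baseline assessment plus an information leaflet. The consequence is confined to a secondary estimate that the article itself calls unpowered, and to its use in planning a definitive trial. No stated sample size or power is invalidated, and the primary outcomes are untouched.

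The size of any shortfall relative to an assessment-only contrast equals the leaflet's own effect, which the documents do not give and which may be zero. The direction, a smaller difference, rests on two assumptions: that the leaflet lowers problem drinking if it does anything, and that only control patients receive it. Severity is low to moderate: the correction is easy, but it changes what the effect estimate can be said to show.

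**What to change.** Reconcile the abstract, Identification and Recruitment of Patients, Intervention Overview and Control Intervention into one definition of the control condition, and state in the same place whether intervention patients also receive the leaflet. Whether it should be given is for the investigators to decide; the text need only agree with itself.

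While the leaflet passage stands, describe the contrast in the objective, the secondary outcome and every effect statement as complex intervention versus baseline assessment plus information leaflet. Add a sentence saying that the pilot difference, and any control-arm proportion, will not be reported or carried into the definitive trial's sample size as an effect against assessment only.

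The cost is wording only. No data collection, sample size or primary outcome changes. The price is a slightly narrower stated contrast.
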